## Abstract

**Background:**

Pregnancy, birth, and motherhood are among the most important events of every woman’s life. Training and participation of mothers in the decision-making process of delivery play an essential role in physical as well as psychosocial preparation of the mother. The healthcare system can improve and enhance the level of care by involving the patient in their self-care process. The aim of the present study is to assess the implementation of the birth plan for the first time in Iran in Tabriz city.

**Methods/design:**

The present study uses a mixed-method with a parallel convergence approach, including both quantitative and qualitative phases. The quantitative phase is a randomized controlled clinical trial performed on 106 pregnant women, 32–36 weeks of pregnancy, referring to Taleghani educational hospital in Tabriz city. The participants will be assigned into intervention and control groups using a randomized block method. A training session will be held about the items of the birth plan checklist at weeks 32–36 of gestation for the participants in the intervention group, whereby a mother-requested birth plan will be developed. It will then be implemented by the researcher after admitting them to the delivery ward. Also, those in the control group will receive routine care. During and after the delivery, the questionnaire of delivery information, neonatal information, and Delivery Fear Scale (DFS) will be completed. Also, a partogram will be completed for all participants by the researcher. The participants in both groups will be followed up until six weeks post-delivery, whereby the instruments of Childbirth Experience Questionnaire (CEQ2.0), Edinburgh’s Postpartum Depression Scale and PTSD Symptom Scale 1 (PSS-I) will be completed six weeks 4–6 weeks postpartum by the researcher through an interview with participants in Taleghani educational hospital. The general linear model and multivariate logistic regression model will be used while controlling the possible confounding variables.

The qualitative phase will be performed to explore the women’s perception of the effect of the birth plan on childbirth experience within 4–6 weeks postpartum. The sampling will be of a purposeful type on the women who would receive the birth plan and will continue until data saturation. In-depth, semi-structured individual interviews would be used for data collection. The data analysis will be done through content analysis with a conventional approach. The results of the quantitative and qualitative phases will be analyzed separately, and then combined in the interpretation stage.

**Discussion:**

By investigating the effect of implementing the birth plan on the childbirth experience of women as well as other maternal and neonatal outcomes, an evidence-based insight can be offered using a culturally sensitive approach. The presentation of the results obtained from this study using the mixed method may be effective in improving the quality of care provided for women during labor.

**Trial registration:**

Iranian Registry of Clinical Trials (IRCT): IRCT20120718010324N58. Date of registration: July 7, 2020. URL: https://en.irct.ir/user/trial/47007/view

## Plain English summary

Women’s choice and control impact on birth experiences. Women’s positive and negative recollections of their birth experiences are related more to feelings and exertion of choice and control than to specific details of the birth experience, birth plan affecting her recollection of the birth experience. The usage of a birth plan is common in developed countries, but it is rather new in developing countries. So far, in Iran, no birth plan has been established. The birth plan can be an effective and important tool to achieve physiological delivery, better control the process of labor and delivery, and enhance satisfaction with childbirth. The present study uses a mixed-method with a parallel convergence approach, including both quantitative and qualitative phases. The present research has two phases: 1) quantitative, which is randomized controlled clinical trial, 2) qualitative with the aim of exploring the women’s perception about the effect of the birth plan on their childbirth experience. The results of the quantitative and qualitative phases will be analyzed separately, and the results will be presented jointly. By implementing the birth plan, the advantages and obstacles of the birth plan in Iranian society can be clarified. In case of observing the positive effect of this plan, its protocol can be provided to planners and policymakers so that they could use it to improve the experience of Iranian women and to enhance maternal and neonatal health outcomes and to increase the active participation of women in the labor and delivery process.

## Background

The birth plan was first put forward in the 1980s in Europe and US in response to the approach of increasing “medicalization of labor” with the aim of improving women’s health, reducing adverse maternal outcomes as well as refining the communication between women and healthcare professionals [1, 2]. The presumption of the birth plan was that it would allow women to express their expectations and needs about the process of childbirth. This plan was a huge movement for reclaiming women’s rights and patient’s reproductive rights. The birth plan has been a communication tool written by pregnant women [3], including their preferences for managing their labor and delivery. It provides different ways for discussion between the care provider and pregnant woman and helps her to achieve better experience of delivery through greater control over their labor. The birth plan is written by women in consultation with the healthcare team; just like the written informed consent sheet, informed and freely chosen decisions should be respected even if they are presented verbally [4, 5].

The WHO recommends the use of birth plan and mostly emphasizes normal processes without interventions [6]. Nevertheless, the birth plan should be beyond a checklist reflecting the preferences and emotions as well as understanding of women about the physiology of birth and women’s need for safety and support [1]. Support and communication during labor enhance the level of satisfaction with the delivery, and this effective communication should begin from the time of admission and constantly continue during labor; when not all things proceed as planned, the information should be actively given in women’s decision-making process [7]. Consequently, the extent of satisfaction with delivery in women grows with the birth plan and improves their delivery experience [8].

The childbirth experience is an important psychological phenomenon postdelivery whose psychological effects lead to various short-term and long-term adverse health outcomes, with the negative experiences of childbirth being well associated with Post Traumatic Stress Disorder (PTSD) and depression [9–12]. The childbirth experienced is stated to be considered a harmful event for some women [13]. PTSD postdelivery is related to the psychological torments of labor. Generally, 5–20% of women may report delivery-associated traumatic events [14]. According to a systematic review, this prevalence of Post-traumatic stress disorder has been reported to be 25% among Iranian women [15]. Research has shown that the childbirth experience may be affected by a wide range of provisions, including support, external control, internal locus of control, as well as obstetrical complications [13–16].

The practice of a birth plan is common in developed countries, but it is rather new in developing countries [17]. So far, in Iran, no birth plan has been established. The birth plan can be an effective and important practice to achieve physiological delivery, improve communication with the healthcare staff, control the process of labor and delivery, improve the maternal and neonatal outcomes, and enhance satisfaction with childbirth. Indeed, the key to achieving these goals is increasing the degree of realization of the birth plan [16–18]. Hence, some policies are required to encourage the use of a birth plan along with executive improvement and adaptation of this plan. It seems that assessment of the effect of implementing a birth plan using a mixed-method approach would help in better understanding the issue. Furthermore, one of the advantages of the birth plan is to decline the cesarean section rate considering the increasing rate of cesarean delivery in Iran [19]. Also, it is expected that a birth plan may support current population policies in Iran [20] by improving neonatal and maternal outcomes. Because, the birth plan establishes a better and easier birth experience for women, leading to adopting vaginal birth over the selective cesarean section. Also, in order for the program to succeed, the healthcare providers should be trained about evidence-based birth care causing the promotion of physiological delivery and developing skills in women to achieve drug-free and intervention-free delivery. Possibly, the implementation of the birth plan could enhance childbirth satisfaction among women.

### Study aim

To assess the effectiveness of the birth plan in women of Tabriz-Iran.

### The specific objectives of the quantitative phase are

Comparing the mean score of childbirth experience in the studied groups (having a birth plan, not having a birth plan)Comparing the mean duration of the active phase of delivery in the studied groups (having a birth plan, not having a birth plan)

### The secondary objectives of the quantitative phase are

Comparing the mean duration of the second stage of delivery in the studied groups (having a birth plan, not having a birth plan)Comparing the mean duration of the third stage of delivery in the studied groups (having a birth plan, not having a birth plan)Comparing the mean score of fear of delivery in the studied groups (having a birth plan, not having a birth plan) by controlling the baseline scoreComparing the frequency of vaginal delivery in the studied groups (having a birth plan, not having a birth plan)Comparing the mean PTSD score in the studied groups (having a birth plan, not having a birth plan)Comparing the frequency of neonatal hospitalization in NICU in the studied groups (having a birth plan, not having a birth plan)Comparing the mean postpartum depression score in the studied groups (having a birth plan, not having a birth plan) by controlling the preintervention depression scoreComparing the mean neonatal Apgar score in the first and fifth minutes in the studied groups (having a birth plan, not having a birth plan)

### The specific objective of the qualitative phase is

Exploring the mothers’ perception of the effect of implementing the birth plan on their childbirth experiences

## Methods/ design

### Study design

The present research is a convergent parallel mixed study with a pragmatic paradigm. We will be able to enrich our findings if we assess the effect of the birth plan through both qualitative and quantitative studies. Therefore, current research has two phases: 1) quantitative, which is a randomized controlled clinical trial, 2) qualitative. The findings of the quantitative and qualitative phases will be analyzed separately, and the final interpretation would benefit from both evidence obtained from both study phases (Fig. 1).

**Fig. 1 Fig1:**
[figure not shown]
Study visual diagram

### Quantitative study

#### Study design

The quantitative phase of the study is a parallel randomized controlled clinical trial. The target population is pregnant women with a gestational age of 32–36 weeks referring to the obstetrics clinic of Taleghani educational hospital, Tabriz, Iran.

#### Inclusion criteria

Minimum age of 18 years, residence in Tabriz city, willingness to undergo vaginal delivery, gestational age of 32–36 weeks, depression score lower than 13 based on EPDS, singleton pregnancy, literacy [reading and writing in Persian], planning for delivery in Taleghani hospital, women with the first and second delivery.

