#### Sample size

The sample size in this study was calculated based on the two variables of “childbirth experience” and “duration of the active phase of labor” using G-power software. Based on the results of the study by Ghanbari Homaei et al. [21] on the variables of childbirth experience and considering m_1_ = 2.71, m_2_ = 3.25 (assuming 20% increase in response to the intervention), sd_1_ = sd_2_ = 0.73, one-sided α = 0.05, and power = 90%, the sample size was calculated 32 participants; considering 10% attrition, the sample size will be 35 in each group. According to the variable of the duration of the active phase of labor and concerning m_1_ = 276.7, m_2_ = 221.4 (assuming 20% reduction in response to intervention), sd_1_ = sd_2_ = 91.3, α = 0.05, and power = 90%, it was calculated as 48 participants, and eventually, it will be 53 as the sample size in each group, given 10% possible attrition. Since the sample size calculated based on the variable of the duration of the active phase of labor would be more extensive. Thus the final sample size was considered 53 in each group.

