#### Randomization and allocation concealment

To allocate the participants to the studied groups, a randomized block method with 4- and 6-blocks will be used with an allocation ratio of 1:1. For allocation concealment, the type of intervention is written in a piece of paper and will be placed inside consecutively numbered opaque envelopes. Random allocation and allocation concealment will be conducted by a person not involving in the sampling and data collection. After the study participants signed the consent form, the relevant envelope will be opened, and the intervention will be implemented.

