### Data analysis

The obtained information at this phase will be analyzed by SPSS 22. To describe the socio-demographic and obstetrics characteristics, descriptive statistics, including frequency (percentage), mean (SD), in case of normality, will be used, while the median (percentile 25 to 75) will be applied for abnormal data. To compare the variables of the childbirth experience, postnatal depression, post-traumatic symptoms, as well as maternal and neonatal outcomes across the studied groups, in bivariate analysis, one-way analysis of variance and chi-square tests will be used; in multivariate analysis, multivariate linear regression or multivariate logistic regression will be employed by controlling the socio-demographic, obstetrics and delivery characteristics.

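### Parity is known before allocation and plausibly affects active-phase duration, but the blocks are not stratified by it, so the unadjusted comparisons lose precision and stay open to chance imbalance

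*Protocol article*

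**What the plan says.** The Inclusion criteria of the protocol article accept both parities: "planning for delivery in Taleghani hospital, women with the first and second delivery". Under Randomization and allocation concealment, "a randomized block method with 4- and 6-blocks will be used with an allocation ratio of 1:1". That section also describes the opaque numbered envelopes and the independent person who prepares the allocation, but it names no stratification factor.

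Active-phase duration is one of the two specific objectives of the quantitative phase ("Comparing the mean duration of the active phase of delivery in the studied groups"). It is also the outcome behind the final sample size: "it was calculated as 48 participants, and eventually, it will be 53 as the sample size in each group, given 10% possible attrition".

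Parity is available in time. It is an eligibility criterion, and the obstetric questionnaire, which the Sampling section places at enrolment, records the number of deliveries.

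The Data analysis section plans two layers. First, "in bivariate analysis, one-way analysis of variance and chi-square tests will be used". Second, it plans multivariable linear or logistic regression controlling socio-demographic, obstetric and delivery characteristics. Parity is not named as a covariate.

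**The concern.** If first labours run longer than second labours, an arm that by chance receives more first deliveries will show a longer mean active phase whatever the birth plan does. With about 50 women per arm, simple chance allows a visible gap in parity, and blocking on order of entry alone does not limit it.

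Two things are at stake. One is how convincing the unadjusted result of the single trial actually run will be, if a baseline table shows unequal parity. The other is precision: variance between parities stays in the error term when it could be taken out at no cost in women.

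The envelope list also differs from most analysis details. A later statistical analysis plan can name a covariate, but it cannot stratify a list that has already been used.

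**Working it through.** **Inputs from the Sample size section.** Active phase: "m_1_ = 276.7, m_2_ = 221.4 (assuming 20% reduction in response to intervention" and "sd_1_ = sd_2_ = 91.3, α = 0.05, and power = 90" (per cent). The planned difference is 276.7 − 221.4 = 55.3, taken as minutes because no unit is given. There are 48 evaluable women per group, or 53 after attrition. A one-sided test is stated only for childbirth experience ("one-sided α = 0.05, and power = 90%, the sample size was calculated 32 participants").

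**Inputs assumed, because the documents give neither.** A 50:50 parity mix, and a gap D between first and second deliveries in mean active-phase duration of 30, 60, 90 or 120 min. The total SD is held at 91.3.

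**Step 1. The plan's own figure.** A difference of 55.3, SD 91.3, one-sided α 0.05 and power 90% give 47 per group by the normal approximation and 48 by the noncentral t. Then 48 × 1.1 = 52.8, so 53. The stated 48 and 53 reproduce. (A two-sided test would need 58 to 59 evaluable per group; that is a separate matter.)

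**Step 2. Chance parity imbalance.** The SD of the between-arm difference in the proportion of first deliveries is √(2 × 0.25/48) = 0.102. The 95% limit is 1.96 × 0.102 = 0.20, or 20 percentage points. From two independent Binomial(48, 0.5) counts, the probability of a gap of 7 or more women is about 0.18. With 30% to 70% first deliveries the SD stays at about 9 to 10 points, so the assumed mix matters little.

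**Step 3. Shift and precision.** The 95% limit of the shift in the unadjusted difference is 0.20 × D. The share of variance due to parity is 0.25 × D²/91.3². The within-parity SD is √(91.3² − 0.25 × D²). Power at 48 per arm is Φ(55.3/(SD × √(2/48)) − 1.645). For SD 91.3 the standard error is 91.3 × √(2/48) = 18.64, and Φ(2.967 − 1.645) = 0.907.

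| Gap D (min) | 95% shift (min) | Share of 55.3 | Variance share | Within-parity SD | One-sided power with parity in model |
|---|---|---|---|---|---|
| 30 | 6 | 11% | 3% | 90.1 | 0.91 |
| 60 | 12 | 22% | 11% | 86.2 | 0.93 |
| 90 | 18 | 33% | 24% | 79.4 | 0.96 |
| 120 | 24 | 43% | 43% | 68.8 | 0.99 |

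Equivalently, the number per group for 90% one-sided power would be 47, 43, 37 or 28 instead of 48.

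**Step 4. Is the shift extra error?** The 95% chance limit of the whole unadjusted difference is 1.96 × 18.64 = 36.5 min. The parity part is √(variance share) × 36.5; for D = 60, √0.108 × 36.5 = 12 min. The shift is therefore a component of the 36.5 min and does not add to it. In 20,000 simulated trials per scenario with no treatment effect, the one-sided type I error was 0.051 for D = 60 and 0.050 for D = 120.

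**Step 5. One unlucky allocation.** Given a 20-point imbalance that favours the intervention, the unadjusted one-sided type I error is about 0.09, 0.15, 0.22 or 0.32 for the four gaps. Allocations in the other direction offset this in the average of Step 4.

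**The case against.** The strongest reply is that the plan already handles most of this. The number of deliveries is collected, and the regression controls obstetric characteristics, of which parity is an obvious one. Once parity is in the model, stratified envelopes add little. With a 50:50 mix, a 20-point imbalance inflates the variance of the adjusted effect by 1/(1 − 0.2²) = 1.04, about 4%, and the average inflation is about 0.102² = 0.01, or 1%. The precision gain thus comes mainly from the model term. That stands.

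It also stands that unstratified permuted blocks are a valid design, and that covariate lists and the choice of primary analysis are commonly left to a fuller document. Their absence from the article is not held against it here. The documents do not state that parity affects labour length. That is a plausible premise, and the size of the gap is an assumption; at 30 min little is gained.

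A reader might infer from the shifts of up to 24 min that the trial is biased, that its false-positive rate is inflated or that 48 and 53 per group are too few. The documents do not support this. The imbalance is random and can go either way, the overall type I error stays near 0.05, and an SD of 91.3 already contains the parity component. Nor do they support the reading that parity is left wholly uncontrolled.

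The reply does not cover the randomisation list. The article fixes its block sizes, ratio and concealment, and it cannot be repaired after use.

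**Conclusion.** The point holds as an inexpensive improvement in efficiency and credibility and does not identify an invalidating error. The ANOVA and chi-square comparisons are open to a chance parity imbalance whose 95% limit would shift active-phase duration by about 6 to 24 min, which is 11% to 43% of the planned effect. They also forgo a gain in power from 0.907 to between 0.91 and 0.99. These ranges rest on an assumed 50:50 mix, assumed gaps of 30 to 120 min, 48 evaluable women per arm, a one-sided 0.05 test and 91.3 as the overall SD. The typical (1 SD) shift is about half the 95% limit. If the true gap is near 30 min, the benefit is slight.

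**What to change.** Prepare two consecutively numbered envelope series, one for first and one for second deliveries, each with the same blocks of 4 and 6 and the same 1:1 ratio. In the Data analysis section, enter parity as a fixed term, as the stratification factor, in the comparison of active-phase duration and of the other outcomes. If allocation has already started, leave the list alone and fix parity as a covariate only; this recovers most of the benefit.

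The cost is a second envelope series prepared by the same independent person and one model term. No extra women or staff are needed. The downside is that incomplete last blocks in two series may leave arm totals a few women apart: a block of 6 holds 3 of each arm, so each series can end at most 3 apart.

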#### Exclusion criteria

Non-cephalic presentation, twins/triplets, having indications for C-section including abnormal presentation, obstetrics problems including placenta previa, post-cesarean vaginal delivery, placental abruption, preeclampsia, high-risk pregnancies such as diabetes, cardiovascular disease, etc. stillbirth, or abnormal fetus.

#### Sample size

The sample size in this study was calculated based on the two variables of “childbirth experience” and “duration of the active phase of labor” using G-power software. Based on the results of the study by Ghanbari Homaei et al. [21] on the variables of childbirth experience and considering m_1_ = 2.71, m_2_ = 3.25 (assuming 20% increase in response to the intervention), sd_1_ = sd_2_ = 0.73, one-sided α = 0.05, and power = 90%, the sample size was calculated 32 participants; considering 10% attrition, the sample size will be 35 in each group. According to the variable of the duration of the active phase of labor and concerning m_1_ = 276.7, m_2_ = 221.4 (assuming 20% reduction in response to intervention), sd_1_ = sd_2_ = 91.3, α = 0.05, and power = 90%, it was calculated as 48 participants, and eventually, it will be 53 as the sample size in each group, given 10% possible attrition. Since the sample size calculated based on the variable of the duration of the active phase of labor would be more extensive. Thus the final sample size was considered 53 in each group.

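### The 48 per group for active-phase duration is a one-sided 5% figure, but the planned ANOVA is non-directional; on a two-sided 5% test the power is about 84 to 87%, not 90%

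*Protocol article*

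**What the plan says.** The Sample size section makes two calculations, both with 90% power.

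- **Childbirth experience:** means 2.71 and 3.25, SD 0.73 in each group. The sidedness is printed: "one-sided α = 0.05, and power = 90%, the sample size was calculated 32 participants".
- **Duration of the active phase:** means 276.7 and 221.4, SD 91.3 in each group. The sidedness is not printed: "α = 0.05, and power = 90%, it was calculated as 48 participants".

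Duration gives the larger number and therefore sets the trial's size: "it will be 53 as the sample size in each group, given 10% possible attrition". Allocation is 1:1.

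For the comparison of groups, the Data analysis section says that "in bivariate analysis, one-way analysis of variance and chi-square tests will be used". Linear or logistic regression with adjustment follows. That section gives neither a significance level nor a sidedness. The specific objectives are worded as comparisons of group means, without a direction.

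**The concern.** A reader who meets α = 0.05 with no qualifier will normally take it as two-sided, the more so because the companion calculation is explicitly labelled one-sided. If 48 is in fact a one-sided number, the power quoted for the endpoint that sets the sample size belongs to a different test from the one named in the analysis. With two groups, the one-way ANOVA F test is identical to the two-sided t test.

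What is at stake is how a null result on duration would be read. It would appear to come from a test with a 10% risk of missing the planned effect, when the risk under the named test is larger.

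**Working it through.** **Inputs (Sample size section).** Duration: difference 276.7 − 221.4 = 55.3, SD 91.3, so d = 55.3 / 91.3 = 0.606. Childbirth experience: difference 3.25 − 2.71 = 0.54, SD 0.73, so d = 0.54 / 0.73 = 0.740. α = 0.05, power 90%, two equal groups.

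**Formula.** The normal approximation is n per group = 2(z_α + z_β)² / d², with z_β = 1.282 and z_α = 1.645 (one-sided) or 1.960 (two-sided). The noncentral t gives the figure for an actual t test.

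**Step 1: reproduce the plan's figures.**

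- Duration, one-sided: 2 × (1.645 + 1.282)² / 0.606² ≈ 46.7, so 47. The noncentral t gives 47.4, so **48**, the stated number.
- Duration, two-sided: 2 × (1.960 + 1.282)² / 0.606² ≈ 57.3, so 58. The noncentral t gives 58.3, so **59**. This does not match.
- Childbirth experience, one-sided: the noncentral t gives 32.0, the stated **32**. Two-sided it gives 39.4, so 40.

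Both stated sizes are therefore one-sided 5% figures, although only one is labelled so.

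**Step 2: power at the planned size.** In the normal approximation, power = Φ(d√(n/2) − z_α). For duration at n = 48, d√(n/2) = 0.6057 × √24 = 2.967. One-sided this gives Φ(1.322) = 90.7%; two-sided it gives Φ(1.007) = 84.3%. The noncentral t figures are:

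| Endpoint | Evaluable per group | One-sided 5% | Two-sided 5% |
|---|---|---|---|
| Duration | 48 | 90.3% | 83.6% |
| Duration | 53 | 92.7% | 87.1% |
| Childbirth experience | 48 | 97.5% | 94.8% |
| Childbirth experience | 53 | 98.4% | 96.5% |

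**Step 3: express the gap for duration.** With 48 evaluable per group, the type II error under a two-sided test is 100 − 83.6 = 16.4%, against the 10% implied. With all 53 evaluable it is 12.9%. A true two-sided calculation at 90% needs 59 evaluable per group; with 10% loss that is 59 / 0.90 = 65.6, so 66 per group (132 in total) against the planned 53 (106).

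**The case against.** **The analysis is never called two-sided.** This is true, and it limits the point. No significance level is stated, and a regression coefficient can be tested one-sidedly. The only sidedness printed anywhere is one-sided, and an analysis plan that is not shown might specify the rest. But the ANOVA F test is non-directional by construction, and a one-sided regression test specified elsewhere would not reconcile it with the sample size.

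**The 84% is conditional.** This also stands. It needs 48 evaluable per group and an unadjusted comparison. Duration is recorded on the partogram during labour, before the six-week follow-up, so the 10% loss may not apply in full; women delivered by caesarean could push the other way. Covariate adjustment may change the power. The documents quantify none of this. Even with no loss, however, the unadjusted two-sided power is 87%, still short of 90%.

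**Power of 84 to 87% may be adequate.** It may well be, but it is not the figure stated.

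**Stronger readings to avoid.** A reader might infer that the trial could not detect harm, such as longer labour. That does not follow: if the analysis is two-sided, as the ANOVA implies, an effect in either direction can be shown. Nor does the protocol say that a birth plan may lengthen labour; it assumes a 20% reduction. A reader might also infer that 48 is an arithmetic error. It is not: it is correct for a one-sided test that is not declared.

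**Conclusion.** The point holds in a limited form. The 48 per group for active-phase duration is a one-sided 5% number without that label, and it does not agree with the non-directional ANOVA named for the analysis. On an unadjusted two-sided 5% test, power for duration is about 84% at 48 evaluable per group and about 87% at 53, a shortfall of roughly 3 to 6 percentage points from the stated 90%.

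This rests on the protocol's own means and SD, equal groups, and a 5% level for the analysis, which the Data analysis section does not itself state. It also takes duration to be among the maternal outcomes analysed by ANOVA.

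The finding does not extend to childbirth experience, so it would be wrong to call the trial as a whole underpowered. No estimate is biased, and a two-sided 5% analysis keeps its type I error. It should be fixed as a misstated power; it is not a threat to validity.

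**What to change.** State the sidedness of α for both sample size calculations and for the analysis, together with the significance level, so that planning and analysis agree.

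With the ANOVA as planned, the simplest consistent wording is that tests are two-sided at 5%. The text would keep 53 per group and give the power as about 84% for active-phase duration with 48 evaluable per group (87% with no loss) and about 95% for childbirth experience with 48 per group. The 90% for duration is then removed or explicitly labelled one-sided.

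The cost is a few words in two sections and a slightly less favourable stated power, with no extra participants. If the authors prefer to keep 90% for duration, they have two alternatives, both dearer: justify a one-sided analysis and replace the F test with a directional one, or enlarge the trial to about 66 per group.
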